***2.7 Side - effects***

Side-effects will be evaluated with a side-effects check list administered biweekly for the first month and then monthly and at end of study. Furthermore, at each weekly meeting the patient will be asked about nausea, vomiting, strange dreams, feelings of depression, and any suicidal ideation.

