***2.2 Patients***

***Number of Patients***. Up to 100 patients will be enrolled in the study and we expect a 10-20% drop out rate. Valid cases for analysis of each variable will be considered subjects who have completed at least 1 post-baseline evaluation on that variable.

***Inclusion Criteria***: Patients will be male or female, 18-65 years of age, with a DSM-IV diagnosis of schizophrenia or schizoaffective disorder determined by best estimate diagnostic approach using research DSM-IV criteria diagnostic checklist, review of chart history and data from structured interviews. Patients will be currently treated with antipsychotic medications, and be judged to have a clinically stable symptom picture and not currently in actue exacerbation of their psychotic symptoms. Patients will have a minimal level of cognitive impairment; defined by a total score of ≤90 on the Repeatable Battery for the Assessment of Neuropsychological Status [RBANS] (The total score for normal subjects is mean±sd 100±15). All schizophrenic patients will either be current cigarette smokers or patients who were regular cigarette smokers in the past, and are not currently smoking daily because they are hospitalized in a non-smoking facility.

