***2.10 Outline of Research Evaluation Schedule***

A) Pre- consent screening -Screening-Chart review of medical and psychiatric diagnosis, and psychopathology and behavior.

*B) Consent*- RBANS, PANSS, CALGARY DEPRESSION, Modified SANS Scale, smoking surges scales

*C)Baseline*- MATRICS Cognitive Battery, Cigarette Dependence Scale, Current Smoking questionnaire, Plasma Sample for Nicotine-Cotinine, Blood Sample for determination of α7 mRNA and DNMT1 and GAD67 mRNA’s in lymphocytes .Side-effect checklist.

DNA Sample may be collected at baseline or any later point if the subject consents to this additional procedure.

*D)Weekly*- weekly interview, with questioning of major changes in psychiatric status or side effects, drug distribution, counting of pills from previous week.

*E)Week 2*- side-effects checklist

*F)Week 4,8*- PANSS, Calgary Depression Scale, side effects checklist, nicotine-cotinine sample, smoking urges scale, side-effects checklist.

*G)Week 8-12* -PANSS, Calgary Depression Scale, side-effects checklist list, Blood Sample for determination of α7 mRNA and DNMT1 and GAD67 mRNA’s in lymphocytes, smoking urges scale , MATRICS Cognitive Battery, Modified SANS, Cigarette Dependence Scale, Current Smoking questionnaire, Plasma Sample of Nicotine Cotinine, side effects checklist.

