***2.11*** ***Criteria for subject termination from study***

Subjects will be terminated from participation in the study if they develop severe nausea or vomiting which does not show tolerance over the first four weeks of treatment, or if they request discontinuation because of this side-effect. Subjects will also be terminated if their PANSS scores show a 35% or greater increase on two consecutive ratings, including at least a 30% increase in positive symptoms, and a CGI score of much worse. They will be also be terminated if the treating physician believes their clinical condition has gotten much worse and requests discontinuation. If the subjects Calgary Depression Scale score increases by >50% on two consecutive ratings, and sum is also > 16, the patient will be terminated from the study. They will also be discontinued if they have persistent suicidal ideation or make a suicidal attempt or gesture. If the patient exhibits a marked increase in psychotic or depressive symptoms from the previous week, which is considered immediately clinically significant and threatening to his life or continued functioning or requiring immediate rehospitalization, the patient will be terminated from the study. If he makes a serious suicidal gesture or attempt in the prior week or expresses definite suicidal intent he will be immediately terminated from the study. Furthermore, subjects have the right to withdraw consent at any time.

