**III STATISTICAL ANALYSIS**

***3.1 General***

The primary dependent outcome variable, will be the average score on all tests of MATRICs battery (converted to T scores from different tests). Secondary cognitive analysis will be the of the hypothesized effects of attention-vigilance, verbal memory, and visual spatial memory. Secondary outcome variables will be cigarette smoking variables( cigarettes smoked, CO, nicotine and cotinine in plasma, smoking scores, Calgary depression scores).The general analysis approach will use a repeated measures analysis of variance. If there are appreciable missing data on measures with several ( >2) sequential testings a mixed model analysis will be used. If the data deviates significantly from normality, a non-parametric approach may be utilized using Wilcoxon matched pair’s signed-ranks, or Friedman’s two way analysis of variance. To examine whether there are differences in effects in patients with different degrees of cigarette smoking, we will compare smoking measures in patients assigned to placebo or active drug, and correlate effects on neuropsychological test changes with the smoking measures described above. Paired T-tests, or repeated measures ANOVA, will be used to analyze differences in the biochemical measures. Pearson or Spearman correlations will be used to examine the relationship between baseline neurochemical measures to cognitive tests performed at baseline, and both baseline neurochemical measure and change in these measures will be correlated with change in neuropsychological test scores. Additional analyses may use these neurochemical measures or changes during treatment as a covariate in an overall repeated measures analysis of variance.

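### The valid-case rule in 2.2 makes no exception for safety, so a patient who leaves early because of a harm can be left out of the analysis of that harm

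*Protocol*

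**What the plan says.** The analysis set is fixed in Protocol 2.2: "Valid cases for analysis of each variable will be considered subjects who have completed at least 1 post-baseline evaluation on that variable". The rule works variable by variable and carves out nothing for safety. The same paragraph says "we expect a 10-20% drop out rate", without timing or reasons.

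Harms are collected in three ways:

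- **Checklist (2.7):** "Side-effects will be evaluated with a side-effects check list administered biweekly for the first month and then monthly and at end of study". Section 2.10 lists it at baseline, week 2, weeks 4 and 8, and weeks 8-12, so the first one after baseline is at week 2.
- **Weekly questions (2.7, 2.10):** "at each weekly meeting the patient will be asked about nausea, vomiting, strange dreams, feelings of depression, and any suicidal ideation". The outline in 2.10 repeats this as a "weekly interview, with questioning of major changes in psychiatric status or side effects".
- **Calgary scale (2.1, 2.5, 2.10):** 2.1 names it as the instrument for depression and emerging suicidal ideation. After baseline it is next scheduled at week 4, with more frequent ratings if the patient worsens (2.5). Its scores are a listed secondary outcome in 3.1: "Secondary outcome variables will be cigarette smoking variables( cigarettes smoked, CO, nicotine and cotinine in plasma, smoking scores, Calgary depression scores".

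Section 2.11 ends participation for "severe nausea or vomiting which does not show tolerance over the first four weeks of treatment, or if they request discontinuation because of this side-effect". The request clause has no minimum time on treatment. Section 2.11 also calls for immediate termination after a serious suicidal gesture or attempt in the prior week, or when definite suicidal intent is expressed.

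**The concern.** For an efficacy score, requiring one post-baseline value is a common convention. For a harm, it makes membership of the analysis set depend on the patient staying long enough to be assessed, and the harm itself can be the reason for not staying. The patient with the clearest event, one who stopped because of it, may then be missing from both numerator and denominator.

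Two windows are open. A patient who asks to stop because of nausea or vomiting before week 2 has no post-baseline checklist. A patient terminated for suicidal behaviour or intent before week 4 has no scheduled post-baseline Calgary rating. At stake is the harm side of the comparison of varenicline with placebo: if such departures are commoner on active drug, the excess is understated.

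**Working it through.** The protocol gives no expected harm rate, so there is no figure of its own to reproduce. The check has two parts.

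**1. Who is excluded, evaluation by evaluation**

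| Evaluation | First scheduled after baseline | Exit that can come earlier (2.11) | Valid case under 2.2? |
|---|---|---|---|
| Checklist | Week 2 | Request to stop because of nausea or vomiting | No, if the patient leaves before week 2 |
| Calgary | Week 4 | Immediate termination for serious suicidal behaviour or intent | No, if before week 4 and no extra rating is done under 2.5 |
| Weekly questions | Week 1 | Either | Yes, once interviewed |

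A patient terminated because severe nausea showed no tolerance over four weeks should already have a week-2 checklist and is not lost.

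**2. How much the checklist rate could move**

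Inputs from the protocol: 30 per arm (3.2) and drop-out *d* of 10% to 20% (2.2). Assumptions: true nausea risk of 30% on varenicline and 10% on placebo; a share *s* of active-arm drop-outs leave before week 2, all with nausea; nobody on placebo is lost this way.

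Excluded patients: k = 30 × d × s. Observed active-arm rate: (9 − k)/(30 − k). The placebo rate stays at 3/30 = 10%, and the true difference is 20 points.

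| s | d | k | Observed active rate | Difference (points) |
|---|---|---|---|---|
| 0 | 10% or 20% | 0 | 9/30 = 30.0% | 20.0 |
| 1/4 | 10% | 0.75 | 8.25/29.25 = 28.2% | 18.2 |
| 1/4 | 20% | 1.5 | 7.5/28.5 = 26.3% | 16.3 |
| 1/2 | 10% | 1.5 | 7.5/28.5 = 26.3% | 16.3 |
| 1/2 | 20% | 3 | 6/27 = 22.2% | 12.2 |
| 1 | 10% | 3 | 6/27 = 22.2% | 12.2 |
| 1 | 20% | 6 | 3/24 = 12.5% | 2.5 |

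Fractional k are expected numbers. Dividing through by 30 gives (0.30 − ds)/(1 − ds), so the percentages do not depend on arm size and would be the same at 50 per arm (the 2.2 ceiling of 100 patients). With an assumed active-arm risk of 40%, the worst-case rates are (12 − 3)/27 = 33.3% and (12 − 6)/24 = 25.0%.

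The direction depends on why patients leave. If the single early leaver had no nausea, the rate would read 9/29 = 31.0%, slightly too high. Understatement needs leaving to be related to the harm.

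No comparable table is given for suicidality, because the document offers nothing on which to base a rate.

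**The case against.** The strongest reply is that safety populations and by-arm harms tables normally belong in the SAP, which is not at hand. That stands as far as it goes: the lack of a harms table in 3.1 is no finding. But the rule in 2.2 is a statement in the protocol, not a gap, and a SAP that counted harms in all dosed patients would have to depart from it.

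The second reply is that little is lost. The rule applies to each variable separately, so anyone interviewed once stays in the analysis of the weekly answers. Section 2.5 calls for extra Calgary ratings on worsening. The reaction to persistent side-effects is framed over two to three weeks in 2.4 and four weeks in 2.11, by which time a checklist should exist. All of this stands and narrows the point to early leavers. It does not close it: the request clause has no minimum time, and 2.11 does not make immediate termination wait for a Calgary rating.

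The third reply is that the large shifts in the table are stacked worst cases. That is correct. The 10-20% is overall drop-out for any reason, and the bottom rows put all of it in the active arm before week 2 with nausea.

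A reader might also infer more than the text supports:

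- *That harms will go unreported.* The data are collected and nothing says they will be withheld. The list in 3.1 is not exclusive; it also leaves out PANSS and SANS, which are plainly outcomes.
- *That suicidal ideation has no analysis.* It is covered in part by the Calgary scale, a listed secondary outcome. Only the separate weekly answer and suicidal events have no named analysis.
- *That strange dreams lead to termination.* Section 2.11 has no such criterion.
- *That any checklist comparison must be biased.* If nobody leaves before week 2, the rule changes nothing.

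**Conclusion.** The point holds in a limited form. As written, the valid-case rule can remove a patient from the analysis of the very harm that made the patient leave: before week 2 for the checklist, and before week 4 for the Calgary scale unless an extra rating is made. Where early leaving is related to the harm, the harm is understated.

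The actual size is unknown. Under the assumed 30% and 10% risks, the difference of 20 points would read 16.3 to 18.2 points if a quarter of drop-outs left this way, and 2.5 to 12.2 points in the extreme case. The moderate rows are a fairer guide to what is at risk than the extreme ones, but neither is an estimate. The case for a change rests on the direction of the bias and the low cost of removing it.

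**What to change.** State in 2.2, and repeat in 3.1, wording to this effect:

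> The valid-case rule does not apply to safety variables. Harms are counted by arm in all patients who took at least one dose of study medication, using the weekly interview answers together with the side-effect checklist. A patient terminated under 2.11 for a side-effect or for suicidality counts as having had that event, whether or not a checklist or Calgary rating was completed.

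The detailed tables can stay with the SAP. The change leaves treatment, visits and the criteria for ending participation as they are.

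The cost is a few sentences. The weekly answers and checklist are already collected. Reasons for termination must be recorded for each patient, since the protocol gives the criteria but does not describe recording which one applied. Reported side-effect rates may come out somewhat higher than under the present rule.

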***2.12 Cigarette Smoking Assessments***

Since smoking is highly prevalent in schizophrenic patients, varenicline has been shown to have antismoking effects in normals and in our preliminary studies also in schizophrenic patients], and it is also possible that nicotine itself has some cognitive effects, we will assess the degree of cigarette smoking in our subjects. Some e Measures will be taken at baseline and last month of study, and others at baseline 4, 8 weeks, and last month of study.

***A). Cigarette Dependence***. To measure at baseline the degree of dependence in current cigarette smokers, we will use the *Cigarette Dependence Scale* (Ettner et al 2003), in an interviewer-administered version.

***B).*** ***Self-report interview assessment***. Self-report of number of cigarettes smoked per day over the last week. Measurements will be made at baseline, 4 weeks, and end of study

***C) Smoking Urges***- A short version Tiffany Smoking urges scale (Cox, Tiffany, Chirsten 2001)

***D)*** ***Nicotine and Cotinine in plasma***. Measurements of plasma nicotine and cotinine will be made in plasma using samples at baseline, week 4 and week 8. It with be analyzed in the Analytical Psychopharmacology Laboratory ([name], director).

*Nicotine and Cotinine Assay*

Nicotine and cotinine are assayed in plasma in the Analytical Chemistry Laboratory at the Nathan Kline Institute for Psychiatric Research, director [name]. The assay is a GC/MS assay, following the procedure described in Davis (Davis1986) with modifications for GC/MS detection. The method involves liquid/liquid extraction with N - ethyl nornicotine and Nicotine D4 and Cotinine D3 as internal standards. Separation is achieved via gas chromatography with a Restek RtX-5 amine 15m 0.25ID 0.50 um df, crossbond 5% diphenyl 95% dimethylpolysiloxane column. Nicotine is run in PCI mode; target ion 163, cotinine is run in EI mode, target ion 98. The detection limit of accurate quantification of nicotine with this assay is 3 ng/ml with intra- and inter-coefficients of variation of 4.7 and 5.9%. Cotinine limit of detection is 5 ng/ml with intra- and inter-assay coefficient of variation of 3.4% and 5.2%.

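### Sections 2.12 B, 2.10 and 3.1 disagree on two secondary smoking measures: the week-4 cigarettes-per-day self-report is required but not scheduled, and CO is a named outcome that nothing collects.

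*Protocol*

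**What the plan says.** **Assessment section.** Protocol section 2.12 (Cigarette Smoking Assessments) lists four measures, A to D. Item B is the cigarette count: "Self-report of number of cigarettes smoked per day over the last week". Its timing is explicit: "Measurements will be made at baseline, 4 weeks, and end of study". The introduction to the section divides the measures into a set taken at baseline and in the last month and "others at baseline 4, 8 weeks, and last month of study", without saying which measure belongs to which set.

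**Schedule.** In section 2.10, the baseline row (C) includes "MATRICS Cognitive Battery, Cigarette Dependence Scale, Current Smoking questionnaire, Plasma Sample for Nicotine-Cotinine". Row F, for weeks 4 and 8, reads "PANSS, Calgary Depression Scale, side effects checklist, nicotine-cotinine sample, smoking urges scale, side-effects checklist". The Current Smoking questionnaire appears again only in row G (week 8-12). The weekly row (D) covers psychiatric status, side effects, drug supply and pill counts. Section 2.7 lists what patients are asked each week, and smoking is not on that list.

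**Analysis.** Section 3.1 gives the secondary smoking outcomes as "cigarettes smoked, CO, nicotine and cotinine in plasma", followed by smoking scores. It offers a mixed model where missing data are appreciable on a measure with more than two sequential testings. Section 2.2 counts a patient as valid for a variable only if the patient has "completed at least 1 post-baseline evaluation on that variable".

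**The concern.** What is collected at which visit is protocol content, and no later analysis plan can recover a value that was never taken. Two parts of this protocol give different instructions for the cigarette count, and a third names an outcome with no source of data.

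Cigarette smoking is in the trial's title, and section 2.1 extends some sites to 12 weeks partly for smoking measures. Section 3.1 also correlates the smoking measures with cognitive change. A week-4 count matters in two ways under the protocol's own rules. It takes the number of testings above two, which 3.1 requires for the mixed model. It also gives a patient who leaves after week 4 a post-baseline value, which 2.2 requires for inclusion. Neither urges (2.12 C) nor plasma cotinine (2.12 D) can stand in for it, because both are separate measures.

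**Working it through.** **Step 1. Set each smoking measure against the schedule.**

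| Measure | Named in | Times required | Times in 2.10 | Gap |
|---|---|---|---|---|
| Cigarettes per day | 2.12 B, 3.1 | Baseline, week 4, end | Baseline, week 8-12 | Week 4 |
| CO | 3.1 only | None stated | None | No measurement |
| Plasma nicotine and cotinine | 2.12 D, 3.1 | Baseline, weeks 4 and 8 | Baseline, weeks 4 and 8, week 8-12 | None |
| Smoking urges | 2.12 C | None stated under C | Consent visit, weeks 4 and 8, week 8-12 | None |
| Cigarette Dependence Scale | 2.12 A | Baseline | Baseline, week 8-12 | None |

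This assumes that the Current Smoking questionnaire in 2.10 is the instrument for the 2.12 B self-report, which the protocol does not say outright. If it is not, the cigarette count appears nowhere in the schedule and the gap is wider. For CO, the section 2.1 overview was also checked: it describes monitoring by questionnaires and plasma nicotine and cotinine, without CO.

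**Step 2. Count testings.** Under 2.12 B there are three, so the more-than-two condition in 3.1 is met. Under 2.10 there are two, so it is not.

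**Step 3. Bound the number of patients affected.** Inputs are N = 30 per arm (section 3.2) and drop-out d = 10% to 20% (section 2.2).

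- All drop-outs per arm, N × d: 30 × 0.10 = 3 and 30 × 0.20 = 6.
- Those whom a week-4 value could retain, N × d × f, where f is the fraction of drop-outs who leave between week 4 and the final assessment. The protocol does not give f. At f = 0 the number is 0, and at f = 1 it is 3 to 6. At f = 0.5, purely as an illustration, it is 1.5 to 3.

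**Step 4. Bound the loss of precision.** Losing a fraction d of an arm multiplies the standard error by 1/√(1 − d): 1/√0.9 = 1.054 and 1/√0.8 = 1.118, so 5% to 12%. This too is a ceiling on what the fix could recover. It takes f = 1, and a week-4 value carries only part of the information in an end-of-study value.

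**Step 5. Ask whether a bias can be computed.** Suppose completers cut c cigarettes per day and drop-outs do not change. One arm's completers-only mean is c, against c(1 − d) for all patients. The ratio 1/(1 − d) is 1/0.9 = 1.11 or 1/0.8 = 1.25 whatever the value of c. That describes a single arm's mean under an assumption about drop-outs. The treatment contrast needs the reduction and the drop-out rate separately for varenicline and placebo, and the protocol gives none of these four figures.

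**The case against.** The strongest reply is that 2.10 calls itself an outline and is visibly incomplete. It omits the spatial navigation task described in 2.6 and the CGI on which a termination criterion in 2.11 relies. Section 2.12 B is the specific instruction, patients are seen at least weekly, and a site that follows 2.12 B will collect the week-4 count. This stands in part: the harm is conditional on sites working from 2.10. It does not remove the contradiction, because a visit schedule is what sites commonly work from.

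A reader might infer that the schedule fails to deliver the smoking outcomes in general. The documents do not support that. Plasma nicotine and cotinine, urges, dependence, and cigarettes per day at baseline and end are all scheduled. Nor is week 4 without any smoking instrument, since the urges scale is listed there.

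A reader might also take 3 to 6 patients per arm, or an overstatement of 11% to 25%, as the size of the damage. These figures count patients who leave before week 4, whom the fix cannot help, and the percentages concern one arm's mean. Row G is moreover a window, so at sites extended to 12 weeks a patient leaving after week 8 may already have completed the questionnaire. Section 2.2 also admits patients who are not smoking daily because they are in a non-smoking facility, so the number with an informative cigarette count is unknown.

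Finally, these are secondary outcomes, and the MATRICS primary outcome is untouched. That is correct and limits the weight of the point.

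**Conclusion.** The inconsistency is real and confined to two secondary measures. One required time point for cigarettes per day is missing from the schedule, and CO has no method, visit or data source.

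If sites follow 2.10, the cigarette count falls from three testings to two, the mixed-model option in 3.1 does not apply to it, and patients who leave between week 4 and the final assessment drop out of its analysis under 2.2. The number affected is between 0 and 6 of 30 per arm, depending on when drop-outs leave, with 3 to 6 as the ceiling at the protocol's own drop-out rates. No figure for bias in the treatment contrast is claimed. The CO problem does not depend on which section sites follow: as the protocol is written, that outcome cannot be reported.

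**What to change.** In row F of section 2.10, add the Current Smoking questionnaire (cigarettes per day over the preceding week) at week 4, to match 2.12 B. Week 8 is not needed to resolve the conflict, because 2.12 B does not name it.

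For CO, choose one of two reconciliations. The cheaper is to remove it from the outcome list in 3.1. If CO is in fact measured, add the method to 2.12 and the visits to 2.10. The protocol does not show whether CO is a leftover or an omitted assessment, so the sponsor has to say which.

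The cost is one short interview item at a visit that already takes place, plus wording in 2.10 and 3.1. Removing CO gives up only an outcome that the present text provides no means of reporting.
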